### 7.2 Dose Justification

Participants will be given instructions on when to take the supplements and prescribed their individualised diet for weight loss. Each diet will be energy and macronutrient matched with a 500 kilocalorie per day deficit based on Harris Benedict equation.

Participants will receive a 1 month supply of supplements during the treatment phase. To maintain the double blind, all Participants from each group will take 2 Ginst15 or placebo before meals, and 2 FBCx or placebo after meals.

All Participants will be asked to return their IP and study product containers (SPC) for reconciliation during the treatment period.

The study Dietitian will provide a written guide as to the specific types of foods and the quantities that can be bought and consumed. Participants will be required to keep a 3 day diet diary every 4 weeks (2 working days and 1 weekend day). See Appendix Q.

### **7.3 Comparator Justification**

Based upon the properties of FBCx and Ginst15, the current double blinded, randomised controlled trial is designed to investigate the beneficial effects of these products in overweight and obese Participants with pre diabetes. It is proposed that these products may over-lap in their function and therefore are being compared in the same trial in the prevention of type 2 diabetes.

### **7.4 Administration**

During the treatment phase for 168 +/-7 days (24 weeks) (6 months) Participants will take a total of 12 pills per day (6 tablets and 6 capsules). Participants will receive a 1 month supply of IP (as described in Figure 7.4). Neither the Participants nor the study staff will know to which tablets or capsules each Participant is randomised, therefore each Participant takes exactly the same amount of capsules and tablets.

#### **FBCx group:**

Participants in the FBCx group will be asked to take 2 placebo capsules prior to each meal, and 2 x 1 gram FBCx tablets directly (within 20 minutes) after each meal 3 times per day. Participants will take a total of 12 pills per day (6 tablets and 6 capsules) for 168 +/-7 days (24 weeks) (6 months).

#### **Ginst15 group:**

Participants in the Ginst15 group will be asked to take 2 x 160 mg Ginst15 capsules prior to each meal, and 2 placebo tablets directly (within 20 minutes) after each meal 3 times per day. Participants will take a total of 12 pills per day (6 tablets and 6 capsules) for 168 +/-7 days (24 weeks) (6 months).

#### **Combined therapy group:**

Participants in the combined therapy group will take 2 x 160 mg of Ginst15 capsules prior to each meal and 2 x 1 gram FBCx tablets directly (within 20 minutes) after each meal 3 times per day. Participants will take a total of 12 pills per day (6 tablets and 6 capsules) for 168 +/-7 days (24 weeks) (6 months).

**Behavioural Management Programme:**

Participants in the standard behavioural management programme alone will be required to take 2 placebo capsules prior to each meal, and 2 placebo tablets directly (within 20 minutes) after each meal 3 times per day. Participants will take a total of 12 pills per day (6 tablets and 6 capsules) for 168 +/-7 days (24 weeks) (6 months).

**Figure 7.4 Four arms of the trial**

|                                |                                                                                                               |                                                                                                                  |
|--------------------------------|---------------------------------------------------------------------------------------------------------------|------------------------------------------------------------------------------------------------------------------|
| FBCx                    | 6x 1 placebo Capsules
[figure not shown]    | 6 x 1 gram FBCx tablets
[figure not shown]   |
| Ginst15                 | 6 x 1 GINST Capsules
[figure not shown]     | 6 x 1 placebo tablets
[figure not shown]     |
| FBCx + Ginst15 combined | 6x 1 GINST Capsules
[figure not shown]    | 6 x 1 gram FBCx tablets
[figure not shown] |
| Placebo                 | 6 x 1 placebo Capsules
[figure not shown] | 6 x 1 placebo tablets
[figure not shown]   |

**7.5 Randomisation**

All treatment groups will include a standard behavioural management programme (nutrition, exercise, and behavioural advice for weight loss) and be allocated to one of four treatment groups (FBCx; Ginst15; FBCx + Ginst15 combined; or placebo using a randomisation programme (FileMaker Pro).

Randomisation will be based on a simple block randomisation.

The Investigators (except for the data manager (Associate [name]), Participants and Sponsor will be blinded as to their treatment allocation. All containers will look identical between the groups other than the additional information of A, B, C or D.

At the commencement of the weight loss maintenance period (month 6), Participants will be randomised to one of three follow-up weight maintenance groups. Random group allocation will be by initial intervention arm and stratified by weight loss during Baseline to 6 months.

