#### 6.3.19.2 Specimen Labelling

At the time of provision of the stool specimen collection kit, a pre-printed label should be placed on the exterior wall of the container. Site staff will write the Participant ID Number, Visit Number, and the Treatment Group Number (1, 2, 3, or 4) on each container. For example, the label should bear the following information (Figure 6.3.19.2) at the time of the return:

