**Figure 6.3.19.2 Specimen Labelling**

|                 |                                   |
|-----------------|-----------------------------------|
| Participant ID  | : XXXXXX                          |
| Date received   | : 16/JUN/2014 (dd/mm/yyyy) |
| Month           | : 12                              |
| Treatment group | : C                               |

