### **6.3.19.4 Collection Method**

The following information and the kit for stool specimen collection will be provided to the Participants at the designated visits (Appendix A). Upon delivery of the specimen to the clinic, the containers will be inspected for integrity and cleanliness. The site staff should make sure that the Participant ID Number, Visit Number, and the Treatment Group Number (A, B, C, D) have been recorded. Stool specimens should be immediately stored in -20°C freezer at the clinic. The stool sample collection log will be completed by the site staff.

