### 6.5.3.3 Study Specific tests

Fasting glucose, HbA1c, Full lipid profile, will be collected at Screening, Month 3, 6 and 12. Fasting glucose, HbA1c, Full lipid profile, Liver enzymes, High-sensitivity C-reactive protein (hsCRP), Apolipoprotein B will be collected at Screening, Month 6 and 12. Routine Stool samples will be collected from all Participants at Baseline, Month 6 and 12.

About 40 Participants (10 from each treatment group) will have an additional weekly stool collection for Microbiota Dynamics assessment over two 8-week periods the first from Month 2 to 4, the second from Month 8 to 10. The Microbiota Dynamics assessment Participants will collect twice weekly and will deliver 8 stool specimens, in visits scheduled for Month 1, 2, 7 and 8. Please see Appendix A for instructions.

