## **7.6 Unblinding**

A treatment code break should only be requested in a medical emergency where the identity of the study treatment is essential for the medical management of the Participant.

When requesting a code break, do not reveal the study treatment to any of the study team, including CRA, Principal Investigator (PI) or pharmacist.

To break the code:

1. Contact the data manager (Associate [name]) and request computer treatment code break.
2. Document the reason for unblinding the Participant in the source notes.
3. Restrict as much as possible the number of people informed of the identity of the study treatment (site and Sponsor level).

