### **11.3 Sample Size**

A total of 400 Participants will be recruited into the study. The study is powered for the smallest difference between two of the groups for each outcome, with the larger sample size

being adopted. This also ensures that the sample size is sufficient to determine the effect of the combination treatment (FBCx and GinST15).

FBCx (a formula based on  $\alpha$ -cyclodextrin): Assuming a mean reduction in fasting total cholesterol from baseline of 0.50 mmol/L in the intervention compared to control group, with a standard deviation (SD) of 0.90 mmol/L and an estimated drop-out rate of 15% (at 6 months), a total of 143 Participants would be required to achieve 80% power to detect a difference between the two groups (at a 2-sided significance level of 2.5%).

Ginst15 (a ginseng extract formula based on Compound K): Assuming a mean reduction in fasting plasma glucose from baseline of 0.47 mmol/L in the intervention compared to control group, with a standard deviation (SD) of 1 mmol/L and an estimated drop-out rate of 15% (at 6 months), a total of 200 Participants would be required to achieve 80% power to detect a difference between the two groups (at a 2-sided significance level of 2.5%).

Based on these calculations, 400 Participants (100 in each group) will be recruited and randomised to one of four treatment groups. All randomised Participants will be included in the final analysis.

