### Oral Examination Sub-study

#### DENTAL DATA COLLECTION SHEET

##### PARTICIPANT

Name: \_\_\_\_\_

Group: \_\_\_\_\_

Age: \_\_\_\_\_

Gender: \_\_\_\_\_

Postcode: \_\_\_\_\_

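### A shared letter per arm on product containers, and the treatment group on every stool jar, let blinded site staff see who shares an arm, so decoding one participant decodes about 100

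*Protocol*

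**What the plan says.** Protocol section 7.5 allocates participants to four product groups by simple block randomisation and keeps the allocation from investigators (other than the data manager), participants and sponsor. On the containers it says: "All containers will look identical between the groups other than the additional information of A, B, C or D".

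The group code is also written on specimens:

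- Section 6.3.19.2: "Site staff will write the Participant ID Number, Visit Number, and the Treatment Group Number (1, 2, 3, or 4) on each container".
- Figure 6.3.19.2, the sample stool label, has a line "Treatment group" filled in with the letter C.
- Section 6.3.19.4 has site staff confirm at return that "the Treatment Group Number (A, B, C, D) have been recorded".
- Section 6.5.3.3: "Routine Stool samples will be collected from all Participants at Baseline, Month 6 and 12".

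Sections 7.1 and 7.4 state that participants and study staff will not know the allocation. Section 7.6 confines code breaks to medical emergencies, routes them through the data manager, and tells the person asking: "do not reveal the study treatment to any of the study team". Section 7.7 lists what the product label carries, including a participant number and a *Bottle code*. It does not define that code and does not mention the letter.

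Section 11.3 gives the size of the groups: "400 Participants (100 in each group) will be recruited and randomised to one of four treatment groups". Section 4 makes this a single-site trial.

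**The concern.** A code that is the same for everyone in an arm masks the treatment but not the grouping. Staff who dispense, weigh, counsel and question participants can sort them into four sets from the containers and jars. The blind then rests on four facts, one per letter. Once one becomes known or is strongly suspected, it is lost for the whole arm. With a code unique to each participant, the same disclosure costs one participant.

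Visible letters also matter for allocation. In blocked randomisation the letters already used in a block limit those still to come, and one team at one site can see the whole sequence.

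Most exposed are the individual dietitian counselling, the investigator's causality judgement for adverse events, the weight measurements and the questionnaires. The group code on a stool jar serves no stated purpose, since participant ID and visit already identify the sample.

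**Working it through.** **1. Do the letters denote arms?** Section 7.1 lists four product presentations, so A to D might be product codes. Two passages exclude that reading: 7.5 says the letter distinguishes the groups, and 6.3.19.4 uses the same four letters for the treatment group. There are four letters and four arms. The coding is inconsistent: numbers in 6.3.19.2, letters in Figure 6.3.19.2 and in 6.3.19.4.

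**2. How often are the codes seen?** A month's supply is dispensed at Baseline and Months 1 to 5 (6.2.1), which is six times per participant. Main-study stool jars come back three times. With no dropout that is 400 × 3 = 1,200 jars carrying a group code, before the extra microbiota samples.

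**3. What does one decoded participant cost?** The plan's group size follows from its own figures: 400 / 4 = 100 per arm.

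- Shared letter: about 100 of 400 decoded. With the 15% dropout at 6 months assumed in 11.3, 100 × 0.85 = 85 of them are still in the study at that point.
- Unique code: 1 decoded.

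**4. How far can the next letter be guessed?** Section 7.5 states no block size, so the sizes below are assumptions. The observer is assumed to know a fixed block size, to see every earlier letter, and to guess the letter with most places left. Each block of size b = 4m holds m of each letter.

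For b = 4 the chances of a correct guess at the four places are 1/4, 1/3, 1/2 and 1, so the rate is (0.250 + 0.333 + 0.500 + 1) / 4 = 2.083 / 4 = 52%.

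For larger blocks, let s be the places left per letter and S their sum. The expected number of correct guesses is G(s) = max(s)/S + Σ (s_i/S) × G(s with one fewer of letter i), and the rate is G/b. An allocation is certain when only one letter is left. For any place that happens with probability 1/(3m + 1), the chance that all 3m places of the other letters come earlier.

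| Block size | Next letter guessed correctly | Next letter certain |
|---|---|---|
| 4 | 52% | 1/4 = 25% |
| 8 | 47% | 1/7 = 14% |
| 12 | 44% | 1/10 = 10% |
| 16 | 42% | 1/13 = 8% |
| 20 | 41% | 1/16 = 6% |
| No visible shared code | 25% | 0% |

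Even at an implausible block of 100, simulation gives 33%, still above chance. All these rates concern the masked letter, not the treatment.

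**The case against.** The strongest defence is section 7.6. Code breaks are for emergencies only, go through the data manager, and are kept from the study team. A reader might infer that a single code break automatically unmasks 100 people. The protocol does not support that: someone must know both the treatment and other participants' letters, and 7.6 is written to prevent it. What stands is narrower. Section 7.6 limits who is told, but it cannot confine a disclosure to one participant while the letter is shared. Nor does it cover inference without a code break, although the protocol gives no arm-specific side-effect profile that would show how likely such inference is.

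A reader might also infer that allocation is predictable and that selective enrolment follows. That goes too far. Block size is unstated, which is proper in a protocol. The best guess is wrong about half the time or more, and it predicts a letter. It has a direction only once a letter is decoded or suspected.

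The "DENTAL DATA COLLECTION SHEET" in Appendix S has a *Group* field, and a reader might take this as another place where the arm is recorded. The field is undefined. The dental examination is repeated at Month 6, when participants enter maintenance groups 1 to 3, so the field could mean those. It covers only consenting sub-study participants. It needs a definition but is not evidence of exposure.

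Finally, the sample size rests on fasting total cholesterol and fasting glucose, which a commercial laboratory measures. Biased measurement of those is unlikely, and differential counselling would again need a decoded letter.

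**Conclusion.** The point holds as a weakness in how the blind is protected. Staff who are meant to be blind can see who shares an arm, because section 7.5 puts the letter on the product and 6.3.19 puts the group on every stool jar. The size is about 100 of 400 participants decoded instead of one, if someone who sees the letters learns or infers one participant's treatment. The secondary effect is a correct guess of the next letter 41% to 52% of the time for blocks of 20 down to 4, against 25% by chance, assuming a fixed and known block size.

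The documents do not show that the blind will be broken, that enrolment will be selective, or that the primary laboratory outcomes will be biased. The sample size in 11.3 is unaffected. The change is still worth making before product is labelled, because exposure to shared letters cannot be undone.

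**What to change.** - **Section 7.5:** replace the arm letter with participant-specific or otherwise unique container codes. Only the data manager, already unblinded, holds the link to arm.
- **Section 7.7:** define *Bottle code* as that unique code, so that 7.5 and 7.7 agree.
- **Sections 6.3.19.2 and 6.3.19.4 and Figure 6.3.19.2:** delete treatment group from stool labels and from the check at return. Participant ID and visit suffice, and the conflict between 1 to 4 and A to D disappears.
- **Block sizes:** vary them and keep them out of site documents.
- **Tasks that need the arm:** the data manager selects the 10 participants per arm for the microbiota cohort (Table 6.5.3.2) and runs the Month 6 randomisation by initial arm (7.5).
- **Appendix S:** state that *Group* must not record the product arm, or delete the field.

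The cost is small but not nil. With one tablet jar and one capsule jar per month, the list covers up to 400 × 6 × 2 = 4,800 containers. Label and form text change, and the data manager takes on some added work. No visit, measurement or sample is added.

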## **7.6 Unblinding**

A treatment code break should only be requested in a medical emergency where the identity of the study treatment is essential for the medical management of the Participant.

When requesting a code break, do not reveal the study treatment to any of the study team, including CRA, Principal Investigator (PI) or pharmacist.

To break the code:

1. Contact the data manager (Associate [name]) and request computer treatment code break.
2. Document the reason for unblinding the Participant in the source notes.
3. Restrict as much as possible the number of people informed of the identity of the study treatment (site and Sponsor level).

## **7.7 Product Labelling**

Each SPC will have 2 perforated labels. One label will stay attached to the SPC while the other half of the label will be detached and placed into the Participant's folder.

The labels contain:

- Study name
- Participant number and initials
- Directions for use
- Storage Instructions
- Bottle code
- Date Dispensed
- Visit number
- Date and Quantity Returned
- Site contact details

- For “clinical trial use only”
- Keep out of reach of children

## **7.8 Handling and Storage of Study Drugs**

All study products are to be stored at room temperature. The study site will confirm receipt of the IP/Placebo in SPC to the study site. The study site will check the shipment and confirm the SPC is intact, not damaged, and can be reconciled with the inventory. Any discrepancies must be acted upon immediately.

The study site must maintain inventory records of the SPC. Records must be made available to the Sponsor and to representatives of regulatory and other governmental bodies, as required by law, regulation or contractual agreement.

The study site must complete an accountability log (medication compliance) for each Participant for both the FBCx/Placebo and the Ginst15/Placebo in each arm - recording the date, the visit, and amount dispensed, as well as the date, the visit and amount returned. The accountability log (medication compliance) must be available for inspection at any time. A copy of the dispensing log will be given to the Sponsor at the end of the study.

At the conclusion of the study, the Investigator and the Sponsor will reconcile all used and unused supplements. The inventory record for returned supplements will be completed. Unused supplements will be destroyed on site following agreement from the Investigator, and a representative of the Sponsor. The Sponsor will keep the original certificate of destruction and copies of this document will be sent to the Investigator.

## **7.9 Dispensing of Study Drugs**

Supplements will be dispensed from the Clinical Trials Unit to the Participants and all dispensing will be recorded in the Clinical Trials Unit IP dispensing log and in the Participant's eCRF. A product accountability log will be utilized to track all IP to the Clinical Trials Unit.

## 8 Adverse Events (AE) and Serious Adverse Events (SAE)

The Investigator is responsible for the detection and documentation of events meeting the criteria and definition of an AE or a SAE as provided in this protocol. During the study, when there is a safety evaluation, the Investigator or site staff will be responsible for detecting AEs and SAEs, as detailed in this section of the protocol.

### 8.1 Definition of an Adverse Event

Any untoward medical occurrence in a Participant temporarily associated with the use of a medicinal product, whether or not considered related to the medicinal product.

An AE can therefore be any unfavourable and unintended sign (including an abnormal laboratory finding), symptom, or disease (new or exacerbated) temporally associated with the use of a medicinal product, whether or not considered related to the medicinal product. For marketed medicinal products, this also includes failure to produce benefits (i.e. lack of efficacy), abuse or misuse.

Examples of an AE include:

- Exacerbation of a chronic or intermittent pre-existing condition including either an increase in frequency and/or intensity of the condition.
- New conditions detected or diagnosed after IP administration even though it may have been present prior to the start of the study.
- Signs, symptoms, or the clinical sequelae of a suspected interaction.
- Signs, symptoms, or the clinical sequelae of a suspected overdose of either IP or a concurrent medication (overdose per se should not be reported as an AE/SAE).

Examples of an AE **do not include** a/an:

- Medical or surgical procedure (e.g. endoscopy, appendectomy); the condition that leads to the procedure is an AE.
- Situations where an untoward medical occurrence did not occur (social and/or convenience admission to hospital).

In this study, AEs may include pre- or post-treatment events that occur as a result of protocol-mandated procedures (i.e. invasive procedures, modification of Participants' previous therapeutic regimen).

## 8.2 Definition of a Serious Adverse Event (SAE)

A serious adverse event is any untoward medical occurrence that, at any dose:

- a) results in death
- b) is life threatening

Note: The term ‘life-threatening’ in the definition of ‘serious’ refers to an event in which the Participant was at risk of death at the time of the event. It does not refer to an event, which hypothetically might have caused death if it were more severe.

- c) requires hospitalisation or prolongation of an existing hospitalisation

Note: In general, hospitalisation signifies that the Participant has been detained (usually involving at least an overnight stay) at the hospital or emergency ward for observation and/or treatment that would not have been appropriate in the physician’s office or out-patient setting. Complications that occur during hospitalisation are AEs. If a complication prolongs hospitalisation or fulfils any other serious criteria, the event is serious. When in doubt as to whether ‘hospitalisation’ occurred or was necessary, the AE should be considered serious.

Hospitalisation for elective treatment of a pre-existing condition that did not worsen from Baseline is not considered an AE.

- d) results in disability/incapacity, or

Note: The term disability means a substantial disruption of a person’s ability to conduct normal life functions. This definition is not intended to include experiences of relatively minor medical significance such as uncomplicated headache, nausea, vomiting, diarrhoea, influenza, and accidental trauma (e.g. sprained ankle) which may interfere or prevent everyday life functions, but do not constitute a substantial disruption.

- e) is a congenital abnormality/birth defect.

Medical and scientific judgement should be exercised in deciding whether reporting is appropriate in other situations, such as important medical events that may not be immediately life-threatening or result in death or hospitalisation, but may jeopardise the Participant, or may require medical or surgical intervention to prevent one of the other outcomes listed in the above definition. These should also be considered serious. Examples of such events are invasive or malignant cancers, intensive treatment in an emergency room or at home for

allergic bronchospasm, blood dyscrasias or convulsions that do not result in hospitalisation, or development of drug dependency or abuse.

